**DATE: February 15, 2019**

**PROTOCOL: 15NRHC**

**REGARDING: Processing Samples for NAD**

**NOTE:**

A deviation from the protocol was made on the matrix used for NAD analysis. NAD was analyzed from whole blood instead of RBCs. The analytical laboratory, Keystone Bioanalytical Inc. confirmed that the method for the analysis was compatible and valid for whole blood.

[name]

[figure not shown]A handwritten signature in red ink, appearing to read '[name]', positioned over the printed name.

Laboratory Manager

KGK Science London

[name]

[name]

[name]

[contact]

[contact]

Email: [contact]

**LIST OF ABBREVIATIONS AND SYMBOLS**

|              |                                           |
|--------------|-------------------------------------------|
| AE           | adverse event                             |
| ALT          | alanine transaminase                      |
| AST          | aspartate aminotransferase                |
| BMI          | body mass index                           |
| °C           | degree Celsius                            |
| CBC          | complete blood count                      |
| Cl           | chloride                                  |
| cm           | centimetre                                |
| EDTA         | diaminoethanetetraacetic acid             |
| e.g.         | for example                               |
| et al | and others                                |
| g            | gram                                      |
| GCP          | Good Clinical Practice                    |
| GGT          | gamma-glutamyltransferase                 |
| i.e.         | that means                                |
| lbs          | pounds                                    |
| ICH          | International Conference of Harmonization |
| IEC          | Independent Ethics Committee              |
| IRB          | Institutional Review Board                |
| K            | potassium                                 |
| kg           | kilogram                                  |
| L            | liter                                     |
| m            | meter                                     |
| mg           | milligram                                 |
| ml           | milliliter                                |
| Na           | Sodium                                    |
| NA           | nicotinic acid                            |
| NAD+         | nicotinamide adenine dinucleotide         |
| NR           | nicotinamide riboside                     |
| RBC          | red blood cells                           |
| REE          | resting energy expenditure                |
| RMR          | resting metabolic rate                    |
| SAE          | serious adverse event                     |
| SOP          | standard operating procedure              |
| SST          | serum separating tube                     |
| TPD          | Therapeutic Products Directorate          |
| ULN          | upper limit of normal                     |
| WBC          | white blood cell                          |

Protocol 15NRHC: A randomized, double-blind, placebo controlled parallel study investigating the effects of Niagen™ (Nicotinamide Riboside) on Niagen™ metabolites in healthy adults

## 1 INTRODUCTION

Precursors to nicotinamide adenine dinucleotide (NAD+), most notably as nicotinic acid (NA, vitamin B3 or niacin), have been shown to be advantageous for the maintenance of heart health and longevity (Carlson & Rosenhamer, 1988; Karpe & Frayn, 2004). Unfortunately, NA supplementation has been reported to cause flushing via activation of the GPR109A receptor (Benyo et al., 2005) and this side-effect has reduced its efficacy, as well as provided a rationale to find alternative precursors for NAD+.

Niagen™ is a commercially-available form of nicotinamide riboside (NR), a NAD+ precursor that does not activate the GPR109A receptor (Chi & Sauve, 2013). Dietary sources of NR are found in yeast extracts, such as beer, as well as in dairy products. Importantly, NAD+ acts as a rate-limiting step for NAD+-consuming enzymes, including sirtuins, poly-ADP ribose polymerases (PARPs), and CD38/157 ectoenzymes, which collectively influence mitochondrial metabolism and cell longevity (reviewed in (Imai & Guarente, 2014)). Interestingly, NAD+ levels have been reported to decrease as we age and this may be associated with defects in mitochondrial signalling, which in turn may accelerate the incidence of age-associated pathologies (Imai & Guarente, 2014). Thus, restoring cellular NAD+ levels with precursors such as NR (i.e. Niagen™) have the potential to reverse these age-associated functional defects, as well as enhance cellular energy production via increased mitochondrial biogenesis. Importantly, urinary methylnicotinamide levels parallel cellular NAD concentrations.

A recent study by Canto *et al.*, (2012) found that synthetically derived NR caused an increase in NAD+ in mouse muscle and liver (Canto et al., 2012). These authors reported that mice challenged with high fat diets did not gain weight and used oxidation of fatty acids as a fuel source and improved insulin sensitivity. Moreover, NR was shown to increase mitochondrial biogenesis in muscle tissue and therefore enhanced the endurance performance of these animals (Canto et al., 2012). Furthermore NR fed mice on either control diets or high fat diets showed increased capacity to maintain body temperature during cold exposure, suggesting an improvement in brown adipose tissue oxidative performance (Canto et al., 2012).

There are numerous proof-of-concept *in vitro* and *in vivo* studies (Bogan & Brenner, 2008; Canto et al., 2012; Khan et al., 2014) that indicate that NR supplementation has beneficial biological effects. However, to date there are no published reports on the safety and bioavailability of NR treatment in humans. We recently conducted a randomized, double-blind, cross-over study to examine the pharmacokinetic effects of Niagen™ dosing in healthy adults ((14NBHC, 2015), unpublished findings). Niagen™ was found to be readily absorbed and exhibit a dose-dependent relationship in human serum and urine. In addition, Niagen™ was well tolerated and presented no toxicity within the acute time-points (1-24h) of the trial. The aim for this study is to investigate the long-term effects of Niagen™ supplementation on Niagen™ metabolite concentrations in blood, urine, and muscle of healthy subjects. Importantly, because urinary N-methylnicotinamide levels are considered the most reliable biomarker for niacin supplementation (Jacob et al., 1998;

Protocol 15NRHC: A randomized, double-blind, placebo controlled parallel study investigating the effects of Niagen™ (Nicotinamide Riboside) on Niagen™ metabolites in healthy adults

Institute of Medicine, 1998), urinary N-methylnicotinamide levels will used as the primary endpoint for assessing Niagen™ metabolism .

Protocol 15NRHC: A randomized, double-blind, placebo controlled parallel study investigating the effects of Niagen™ (Nicotinamide Riboside) on Niagen™ metabolites in healthy adults

## **2 STUDY OBJECTIVES**

The objective of this study is to evaluate the effect of repeated doses of Niagen™ (Nicotinamide Riboside, NR) on Niagen™ metabolite concentrations in blood, urine, and muscle in healthy adults.

### **Primary outcome:**

The difference in urinary methylnicotinamide levels between placebo and Niagen™ (100mg, 300mg, and 1000mg) treated subjects after 8 weeks of supplementation.

### **Secondary outcomes:**

1. The rate of increase in urinary methylnicotinamide levels between placebo- and NR (100mg, 300mg, and 1000mg)-treated subjects after 8 weeks.
2. The difference and rate of increase in other NR metabolites (see section 6.7) levels in blood between placebo- and NR (100mg, 300mg, and 1000mg)-treated subjects after 8 weeks.
3. The difference and rate of increase in other NR metabolites (see section 6.7) levels in urine between placebo- and NR (100mg, 300mg, and 1000mg)-treated subjects after 8 weeks.
4. The difference in other NR metabolites (see section 6.7) levels in muscle between placebo- and NR-(100mg, 300mg, and 1000mg)-treated subjects after 8 weeks

### **Exploratory outcomes**

1. Change in Resting Energy Expenditure (REE) relative to placebo after 8 weeks of supplementation
2. Changes in blood levels of branched amino acids relative to placebo after 8 weeks of supplementation
3. Changes in blood levels of high sensitivity C-reactive protein (hsCRP) relative to placebo after 8 weeks of supplementation

### **Safety outcomes:**

1. The difference in vital signs, hematology and clinical chemistry parameters including HDL, LDL, triglycerides, and total cholesterol between placebo and Niagen™.
2. The difference in the incidence of adverse events between the placebo and Niagen™.

Protocol 15NRHC: A randomized, double-blind, placebo controlled parallel study investigating the effects of Niagen™ (Nicotinamide Riboside) on Niagen™ metabolites in healthy adults

### 3 STUDY DESIGN

[figure not shown]

This will be a randomized, double blind, placebo controlled, 4-arm parallel study that will investigate the effect of Niagen™ supplements in healthy subjects on Niagen™ metabolite concentrations in urine, blood, and muscle in healthy males and females.

The planned sample size for this study is 140 healthy males or females, with 35 subjects randomized equally to each of the four study arms in a double-blind manner at a ratio of 1:1:1:1.

| Study Arm      | Subject Number |
|----------------|----------------|
| Niagen™ 100mg  | N = 35         |
| Niagen™ 300mg  | N = 35         |
| Niagen™ 1000mg | N = 35         |
| Placebo        | N = 35         |
| Total   | N = 140 |

In order to evaluate primary, secondary, exploratory, and safety outcomes, study assessments will be conducted at baseline and all study visits. At each visit to the clinic, whole blood (which will be centrifuged and separated into WBC, RBC and plasma fractions) and urine will be collected from each participant for NR metabolite and creatinine analysis. REE will also be calculated at baseline and all subsequent clinic visits using indirect calorimetry. A muscle biopsy will be collected at baseline and end of study (week 8).

The study will be conducted at a single site in London, Ontario.

Protocol 15NRHC: A randomized, double-blind, placebo controlled parallel study investigating the effects of Niagen™ (Nicotinamide Riboside) on Niagen™ metabolites in healthy adults

#### **4 SELECTION OF STUDY POPULATION**

This study will include 140 healthy adult volunteers. Each volunteer will have to fulfill the inclusion criteria and not meet any of the exclusion criteria as described in sections 4.1 and 4.2.

##### **4.1 Inclusion Criteria**

1. Healthy Male or female 40-60 years of age
2. BMI 25-30 kg/m^2
3. If female, subject is not of child bearing potential, which is defined as females who have had a hysterectomy or oophorectomy, bilateral tubal ligation or are post-menopausal (natural or surgically with > 1 year since last menstruation)

OR

Females of childbearing potential must agree to use a medically approved method of birth control and have a negative urine pregnancy test result. Acceptable methods of birth control include:

- Hormonal contraceptives including oral contraceptives, hormone birth control patch (Ortho Evra), vaginal contraceptive ring (NuvaRing), injectable contraceptives (Depo-Provera, Lunelle), or hormone implant (Norplant System)
  - Double-barrier method
  - Non-hormonal intrauterine devices
  - Vasectomy of partner
4. Healthy as determined by laboratory results, medical history, and physical exam
  5. Agrees to comply with study procedures
  6. Agrees to maintain current level of physical activity throughout the study and avoid exercising on the day of study visits 3 to 7 (prior to the visit).
  7. Agrees to refrain from consuming caffeine (i.e. coffee) on the days of study visits 3 to 7 (prior to the visit)
  8. Agrees to avoid taking Vitamin B3 (niacin, nicotinic acid, niacinamide) supplements or multivitamins 14 days prior to randomization and for the duration of the study period
  9. Has given voluntary, written, informed consent to participate in the study
  10. Agrees to avoid foods that contain high amounts of tryptophan and niacin and limit their ingestion of foods containing moderate amounts of tryptophan and niacin.

##### **4.2 Exclusion Criteria**

1. Women who are pregnant, breastfeeding, or planning to become pregnant during the course of the trial.
2. Alcohol use >2 standard alcoholic drinks per day
3. History of alcohol or drug abuse within the past year
4. Medicinal use of marijuana
5. Diabetes (Type I or Type II)
6. Active peptic ulcer disease
7. Subjects taking lipid lowering drugs and blood pressure medications
8. History of renal and/or liver disease
9. History of pellagra or niacin deficiency

Protocol 15NRHC: A randomized, double-blind, placebo controlled parallel study investigating the effects of Niagen™ (Nicotinamide Riboside) on Niagen™ metabolites in healthy adults

10. Significant or untreated medical disorders including recent myocardial ischemia or infarction, unstable angina, uncontrolled hypertension, AIDS, malignancy, and neurological disorders including epilepsy, and recent cerebrovascular disease
11. Subjects with or who had recently experienced a traumatic injury, inflammation, infections or had undergone surgery.
12. Use of natural health products containing NR within 14 days prior to randomization and during the course of the study
13. Unstable medical conditions as determined by the Qualified Investigator
14. Clinically significant abnormal lab results at screening (e.g. AST and/or ALT > 2 x ULN, and/or bilirubin > 2 x ULN) will be assessed by the Medical Investigator
15. History of or current diagnosis of any cancer (except for successfully treated basal cell carcinoma) diagnosed less than 5 years prior to screening. Subjects with cancer in full remission more than 5 years after diagnosis are acceptable
16. Participation in a clinical research trial within 30 days prior to randomization
17. Allergy or sensitivity to study supplement ingredients
18. Allergy or sensitivity to lidocaine
19. Bleeding disorder
20. Serum creatinine  $\geq 130\mu\text{mol/L}$  for males and  $\geq 125\mu\text{mol/L}$  for females
21. Individuals who are cognitively impaired and/or who are unable to give informed consent.
22. Any other condition which in the Investigator's opinion may adversely affect the subject's ability to complete the study or which may pose significant risk to the subjects

#### **4.3 Concomitant Medications**

Participants who are currently taking any prescribed medications must agree to maintain their current method and dosing regimen during the course of the study.

Use of blood pressure and cholesterol lowering medications are not permitted.

Use of natural health products/dietary supplements containing niacin (nicotinic acid) or nicotinamide within 14 days of randomization or during the study is not permitted.

#### **4.4 Early Withdrawal**

##### **Personal reasons**

As stated in the Informed Consent Form, a participant may withdraw from the study for any reason at any time.

##### **Removal by PI:**

Participant discontinuation should be considered at the discretion of the Qualified Investigator. The circumstances of any discontinuation have to be documented in detail in the participant file and final report. If possible, the evaluations planned for the end of treatment will be carried out at the time when the participant is withdrawn from the study. A participant leaving the study prematurely will NOT be replaced by another. It is understood by all concerned that an excessive rate of withdrawals can render the study un-interpretable; therefore, unnecessary withdrawal of participants should be avoided.

Criteria for removal of participants from the study will include:

##### **Clinical reasons**

Protocol 15NRHC: A randomized, double-blind, placebo controlled parallel study investigating the effects of Niagen™ (Nicotinamide Riboside) on Niagen™ metabolites in healthy adults

A participant may be withdrawn from the study if, in the opinion of the Qualified Investigator, it is not in the participant's best interest to continue. Any participant who experiences a serious adverse event (SAE) may be withdrawn from the trial at the discretion of the Qualified Investigator. A participant will also be withdrawn due to adverse events causing clinically significant illness or the need for prohibited medication(s) during the trial. Any female subject who becomes pregnant during the course of the trial will be withdrawn.

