#### **7.2.2 Treatment and Follow-up of Laboratory Abnormalities**

In the event of subject-initiated withdrawal or clinically significant unexplained abnormal laboratory test values, the subject will be withdrawn from the treatment and will remain in the study and be required to attend all remaining study visits as part of a safety arm.

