### 8.3 Analysis Plan

An effectiveness analysis based on the modified intent-to-treat population and an efficacy analysis based on the per protocol population will be performed. Variables will be tested for normality and log-normality. Log-normally distributed variables will be analyzed in the logarithmic domain. Non-normal variables will be analyzed by appropriate non-parametric tests.

All missing values in the intent-to-treat (effectiveness) analysis will be imputed with the most recent previously-available value (LOCF, or "last-observation-carried-forward" imputation). No imputation will be performed for missing values of safety variables.

For each numerical endpoint, a summary table will be prepared with a variety of summary statistics including mean, standard deviation, median, minimum value, and maximum value for each time point-treatment pairing. In order to account for any a priori differences between groups, the summary statistics of the changes from baseline will also be provided. For parameters requiring the logarithmic transformation, the summary statistics will be provided as non-transformed values. Mean values will be displayed as graphs, with a separate line for each product, and error bars indicating  $\pm 1$  SEM. Mean changes from baseline will be graphed similarly.

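### Sections 4.4 and 7.2.2 conflict on whether a participant who comes to need a lipid-lowering drug stays for follow-up, and blood-pressure cases have no retention rule, so later blood pressure and lipid values go missing according to outcome

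*Protocol*

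**What the plan says.** Five parts of the protocol bear on this.

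- **Section 4.4, clinical reasons**, among the criteria for removal from the study: "A participant will also be withdrawn due to adverse events causing clinically significant illness or the need for prohibited medication(s) during the trial". The wording is mandatory, whereas the neighbouring rule on serious adverse events is discretionary.
- **Section 4.3**: "Use of blood pressure and cholesterol lowering medications are not permitted". These are the only prescription classes that the section prohibits. Its other prohibition concerns supplements containing niacin or nicotinamide.
- **Section 2, safety outcomes**: outcome 1 is "The difference in vital signs, hematology and clinical chemistry parameters including HDL, LDL, triglycerides, and total cholesterol between placebo and Niagen™". No time point is given. Outcome 2 is "The difference in the incidence of adverse events between the placebo and Niagen™".
- **Section 7.2.2**: "In the event of subject-initiated withdrawal or clinically significant unexplained abnormal laboratory test values", product is stopped but the participant stays in the study and attends every remaining visit for safety follow-up.
- **Handling of the data**: under removal by the investigator, section 4.4 adds: "If possible, the evaluations planned for the end of treatment will be carried out at the time when the participant is withdrawn from the study". Section 8.3 asks for summary statistics of each numerical endpoint by time point and treatment, and says: "No imputation will be performed for missing values of safety variables".

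**The concern.** The event that removes a participant can be a bad value of a variable being compared. Someone whose blood pressure or lipids worsen as an adverse event, to the point of needing a drug for it, meets the section 4.4 criterion and leaves. Participants without such worsening stay and supply the later values. If one dose of the product raised blood pressure or lipids, that arm would lose more of its highest values than placebo would, and the later-visit difference would shrink toward zero. For a safety outcome that is the unfavourable direction.

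The protocol already has a way to avoid this loss, the continued follow-up in section 7.2.2. However, it covers only some of these participants, and for those it does cover, section 4.4 says the opposite.

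**Working it through.** **Which rule applies to whom**

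| Case | Section 4.4 | Section 7.2.2 | Result |
|---|---|---|---|
| Clinically significant, unexplained lipid abnormality; adverse event creates a need for a cholesterol lowering drug | Removed from the study | Product stopped, all remaining visits attended | Contradiction |
| Lipid abnormality with an explanation, same need | Removed | Not covered | No retention |
| Blood pressure rise, same need | Removed | Not covered: not a laboratory value | No retention |
| Participant withdraws by own choice | May leave at any time | Remaining visits attended | Retained by the wording of 7.2.2 |

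The first row is a real overlap. Section 7.1.4 does not name lipids in its parameter list, but its rule extends to any laboratory result. It counts a result as clinically significant when a change in concomitant therapy is required. A lipid result that calls for a new drug can therefore trigger both sections.

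**What data would exist**

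Blood pressure and the lipid panel are scheduled at Days 0, 7, 14, 28 and 56. A participant removed after Day 14, for example, has values to that point and, if possible, one set at withdrawal. The protocol does not say where the withdrawal set enters a table organised by time point. With no imputation, the Day 28 and Day 56 cells are empty.

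**Size**

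The protocol states no blood pressure or lipid SD, effect or medication rate, so there is no figure to reproduce. What follows is illustration.

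*Per participant.* 35 per arm with 20% attrition leaves 35 × 0.8 = 28. Removing one person whose value exceeds the mean of the others by E lowers the arm mean by E / 28. For E = 20 to 30 mmHg (assumed) that is 20 / 28 = 0.7 to 30 / 28 = 1.1 mmHg.

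*Simulation A.* Assumed: systolic mean 125, SD 12, correlation between visits 0.7, baseline below 140, removal when two consecutive on-treatment visits up to Day 28 average at or above a threshold.

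| True difference | Threshold | Removed, active / placebo | Observed at Day 56, removed participants missing | With the value at the triggering visit used |
|---|---|---|---|---|
| 5 | 140 | 16% / 6% | 3.7 | 5.4 |
| 5 | 145 | 6% / 2% | 4.3 | 5.2 |
| 5 | 150 | 2% / 0.3% | 4.7 | 5.1 |
| 8 | 140 | 25% / 6% | 5.7 | 8.6 |
| 8 | 145 | 11% / 2% | 6.7 | 8.5 |
| 8 | 150 | 4% / 0.3% | 7.5 | 8.2 |

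*Simulation B.* Assumed: mean 122, SD 10, removal on the Day 28 value alone. A true 5 is observed as 4.3, 4.9 and 5.0 at thresholds 140, 150 and 160. With the Day 28 value used for those removed it is 5.3, 5.1 and 5.0.

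*Yardstick.* Under simulation A's SD and correlation, the baseline-adjusted standard error of a 28-versus-28 comparison is 12 × √(1 − 0.7²) × √(2/28) = 2.3 mmHg. The shrinkage of a true 5 in that model is 0.3 to 1.3 mmHg, below one standard error.

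**The case against.** The strongest reply is that the protocol already limits the damage.

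- The removal criterion sits under a paragraph that plans end-of-treatment evaluations at withdrawal. These include blood pressure and lipids, and both simulations show that using such a value removes the shrinkage. This stands as to size. It does not close the gap, because collection is conditional and no use of the value is stated.
- The participants are not invisible. They remain in the Safety Population (section 8.2), their earlier visits are summarised, the triggering adverse event counts in safety outcome 2, and section 8.3.1 lists each discontinuation with its reason. All of this stands. It shows that the event happened, but it does not restore the later blood pressure and lipid values.
- Leaving safety data unimputed is defensible, and details of safety tables may properly sit in a statistical analysis plan. Both points stand, and neither is criticised here. The contradiction between two protocol sections on who keeps attending is not something an analysis plan can settle.

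A reader might infer more: that everyone with a poor blood pressure or lipid response must leave, that a Day 56 safety comparison is therefore biased by a known amount, and that the product will look safer than it is. The documents do not support that. Section 7.2.2 retains some lipid cases, outcome 1 names no Day 56 comparison, section 8.3.2 describes only adverse event reporting, and every mmHg figure above rests on assumed inputs.

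**Conclusion.** The point holds as a contradiction and a gap. Sections 4.4 and 7.2.2 give opposite instructions for a participant whose clinically significant, unexplained lipid abnormality creates a need for a prohibited drug. A participant in the same position because of blood pressure has no retention rule at all. Taken with conditional collection at withdrawal and no imputation, later blood pressure and lipid summaries by time point omit these participants for a reason tied to the outcome.

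The direction is toward no difference from placebo. The size cannot be derived from the protocol. On the assumptions shown it runs from almost nothing to about a quarter of a true 5 mmHg difference ((5.0 − 3.7) / 5.0 = 26%), the upper end needing a low medication threshold and no use of withdrawal-visit values. With the withdrawal evaluation normally obtained and used, the effect is probably small. No illustration was made for lipids, where section 7.2.2 may retain some cases. The amendment is worthwhile because it is cheap and the outcome is a safety one.

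**What to change.** 1. Reconcile section 4.4 (clinical reasons) with section 7.2.2, so that one statement says who remains in follow-up. No treatment or stopping rule is proposed here.
2. Separate stopping product from data collection. Ask participants withdrawn because an adverse event created a need for a blood pressure or cholesterol lowering drug, with their consent, to attend the remaining scheduled visits for vital signs and lipids.
3. State in section 8.3 that withdrawal-visit values and off-treatment values enter the blood pressure and lipid summaries, labelled as such.
4. Report by arm, alongside safety outcome 1, the number of participants who needed blood pressure or lipid lowering medication.

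The cost is amendment wording in sections 4.4, 7.2.2 and 8.3, one extra table row, and a few already scheduled visits kept. No participants are added. The drawback is that values taken after product is stopped, or after medication is started, do not show the effect of continued product use, so they need separate labelling and cautious reading.
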